# CONSENT, SELECTION, SCREENING, and ENROLLMENT

Study patients will be served on first come first serve basis as per the protocol.

Consenting and eligible patients will be enrolled as soon as possible in a COCID-19 management facility and the study intervention begun. It is important that symptomatic patients suspected for COVID-19 on clinical grounds are quickly evaluated for eligibility. It is important to enroll the patient as close to the onset of symptoms as possible. As described above, this study is dealing with patients of COVID who are ‘non-emergent’ which means mild and moderate disease (pneumonia) which does not require emergency or critical care (see section on inclusion and exclusion criteria).

An ‘Patient Information Sheet’ (Appendix F) in the language understood by the patient will be provided to each patient for study and discussion prior to enrollment. The information fact sheet will describe the overall design of the study and the rationale, benefit and side effect profile of the study drug interventions, and other aspects of the study.

Patients will be selected from the outpatient or inpatient facility in COVID-19 medical centres/ hospitals. The study will be explained to the volunteer patients and those willing to sign the informed consent (Appendix G) will be screened for eligibility as per the inclusion and exclusion criteria in the protocol.

Though it will be preferable to enrol patients with diagnosis confirmed by a positive RT-PCR assay using a nasal or throat swab in a standardized procedure, a patient with a clinical diagnosis of COVID- 19 as described below will be eligible.

Eligible patients will be enrolled using a simple randomization table (provided to the investigator) in a block of 20 patients each to either of the two study arms - SOC plus Ayurveda drug or SOC. As the target sample size is 70 patients in each arm, the first block of randomized allocation will be of 10. The study randomization will be carried out by the investigator.

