**i. Eligibility:**

1. **Inclusion Criteria:**
2. Typical clinical presentation of acute onset febrile illness with cough and a RT_PCR based laboratory confirmation test for COVID-19
3. Patients with either sex, 18 to 75 years age
4. Patients with mild to moderate patients
5. All patients must agree not to share medication
6. Patients willing to participate and sign an informed consent
7. Exclusion Criteria:
8. Patients suffering from severe COVID-19 Disease as judged by a physician and fulfilling at least two of the following three criteria* (i) Respiratory distress at room ambience (≥30 breaths per min) (ii) Oxygen saturation at rest ≤93% (peripheral digital arterial oxymetry) and requiring oxygen support for over one hour to normalize (iii) Any of the known COVID-19 complications and emergency procedures which may require shift/admission in intensive care unit such as respiratory failure, adult respiratory distress syndrome, requirement of oxygen support for over 1 hour, requirement of mechanical ventilation, septic shock, or severe non-respiratory organ dysfunction or failure.
   (Adapted and modified from the reference: Yang Liu et al. Lancet Infect Dis 2020, 2020 https://doi.org/10.1016/ S1473-3099(20)30232-2)
9. Chronic, Severe, Unstable, Uncontrolled co-existent medical illness such as Diabetes, Hypertension, Cardiac disorders, liver, kidney disorders and lung disorders or other disease of concern which may put the patient at increased risk during the study
10. History of immunosuppression: solid organ or bone marrow transplant, use of immunosuppressive antimetabolic and biologic agents, intrinsic immunodeficiencies, HIV infection.
11. Active cancer diagnosis, on palliative treatment or requiring current therapy with antimetabolic agents, immunotherapy or radiotherapy.
12. Patients on parenteral nutrition
13. Patients with known sensitivity or contraindication to any of the ingredients of study medication
14. History of bleeding haemorrhoids, haemoptysis, acid peptic diseases, ulcers and pulmonary diseases (tuberculosis, asthma, etc.)
15. Patients who are likely to worsen or planed ICU admission or ventilator support due to any reason
16. Pregnancy and lactation
17. Participation in a drug interventional clinical drug trial of any nature in the three month period preceding onset of COVID-19
18. Participation in any other clinical trial of an experimental agent treatment for COVID-19

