# 3. RATIONALE FOR PROPOSED STUDY

The absence of specific drug treatment and lack of vaccine is a critical gap in the knowledge of COVID-19 pandemic (38). And in this regard it is important to refer to a seminal paper published on the ‘responsibility and accountability of conducting standard research including randomized clinical drug trials by the medical community’ in times of epidemics, and the authors have used the recent Ebola virus epidemic in Africa to highlight their contention (39).

The Ministry of AYUSH, GOI has recommended the self-care guidelines for preventive health measures and boosting immunity with special reference to respiratory health based on Ayurvedic literature and scientific publications. However, this advisory does not claim to be treatment for COVID-19. The role of Ayurveda Rasayana as an immunomodulator is well known and should be investigated in COVID-19 (40). In this protocol, we describe the rationale for using three Ayurveda herbal formulations individually to treat COVID-19 as an add-on/adjunct therapy to standard of care. The three Ayurveda formulations are AYUSH-64, Sanshamani Vati Plus and Yashtimadhu. In India the guidelines issues by the Ministry of Health and Family Welfare are generally followed as standard of care (See above, Section 2.6 (20). It is difficult if not impossible to expect a uniform nature of standard of care in the study site hospitals in this study.

Patients suffering from symptomatic Mild to Moderate COVID-19 will be selected for this study. By ’Mild to Moderate’ it would essentially mean that patients do not require any of the emergency measures that are advocated for severe and life-threatening cases of COVID-19. The latter would include complications of progressive lung disease, septicemia, shock and other complications (see Table 3). The mild to moderate cases of COVID-19 will belong to the categories of ‘Mild’ and ‘Pneumonia’ as described by WHO (See WHO Table on Syndromes associated with COVID-19 shown in Section 2.6 above). Mere need for supplement oxygen using non-invasive means will not negate the classification of mild to moderate COVID-19.

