# 10. PATIENT POPULATION

The patients will be largely drawn from COVID-19 clinics and outpatients in various medical colleges and hospitals. All patients will be admitted in the hospital for standard care and those willing to participate in the study will be screened and enrolled as described above. Only patients with mild to moderately severe symptoms will be selected as described above. If the patients progress to a severe stage of illness as described below, they will be withdrawn from the study but the investigator will be encouraged to follow the patient ill study completion at week 12 and during this period record the hospital management, course of illness , final outcome and post recovery health status as described in this protocol.

- 1. Inclusion Criteria:

1. Typical Clinical presentation of acute onset febrile illness with cough and a RT_PCR based laboratory confirmation test for COVID-19
2. Patients with either sex, 21to 69years age
3. Patients with Mild to Moderate COVID-19 as described below
4. All patients must agree not to share medication
5. Patients willing to participate and sign an informed consent
   Note: The criteria for mild to moderate COVID-19 are based on the WHO recommendations (See Section 2.5 above with WHO Table on clinical syndromes of COVID-19 and include Mild disease and Uncomplicated Pneumonia but not severe disease which requires any form of intensive care such as invasive techniques for supplemental oxygen or ventilation and life support systems, and absence of any life threatening complications (such as severe respiratory failure, adult respiratory distress syndrome, septicaemia shock and other complications shown in Table 3 above)
   1. Exclusion Criteria

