**INCLUSION CRITERIA:**

|  |  | YES | NO |
| --- | --- | --- | --- |
| 1 | Typical Clinical presentation of acute onset febrile illness with cough and a RT_PCR based laboratory confirmation test for COVID-19 |  |  |
| 2 | Typical Clinical presentation of acute onset febrile illness with sore throat and dry cough with or without shortness of breath in a patient from a known ‘hot spot’ area or in close contact with a confirmed COVID 19 case with a negative laboratory test for COVID 19 and H1N1 influenza |  |  |
| 3 | Patients with either sex, 18 to 75 years age |  |  |
| 4 | Patients with mild-moderately severe disease |  |  |
| 5 | All patients must agree to refrain from donating blood while on study drug and for 28 days after discontinuation from this study treatment |  |  |
| 6 | All patients must agree not to share medication |  |  |
| 7 | Patients willing to participate and sign an informed consent |  |  |

[figure not shown]

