**EXCLUSION CRITERIA:**

|  |  | YES | NO |
| --- | --- | --- | --- |
| 1 | Patients suffering from severe COVID-19 Disease as judged by a physician and fulfilling at least two of the following three criteria* (i) Respiratory distress at room ambience (≥30 breaths per min) (ii) Oxygen saturation at rest ≤93% (peripheral digital arterial oxymetry) and requiring oxygen support for over one hour to normalize (iii) Any of the known COVID-19 complications and emergency procedures which may require shift/admission in intensive care unit such as respiratory failure, adult respiratory distress syndrome, requirement of oxygen support for over 1 hour, requirement of mechanical ventilation, septic shock, or severe non-respiratory organ dysfunction or failure. |  |  |
| 2 | Chronic, Severe, Unstable, Uncontrolled co-existent medical illness such as Diabetes, Hypertension, Cardiac disorders, liver, kidney disorders and lung disorders or other disease of concern which may put the patient at increased risk during the study |  |  |
| 3 | History of immunosuppression: solid organ or bone marrow transplant, use of immunosuppressive antimetabolic and biologic agents, intrinsic immunodeficiencies, HIV infection. |  |  |
| 4 | Active cancer diagnosis, on palliative treatment or requiring current therapy with antimetabolic agents, immunotherapy or radiotherapy. |  |  |
| 5 | At least one fever every 24 hours for > 72h |  |  |
| 6 | Patients on parenteral nutrition |  |  |
| 7 | Patients with known sensitivity or contraindication to any of the ingredients of study medication |  |  |
| 8 | History of bleeding haemorrhoids, haemoptysis, acid peptic diseases, ulcers and pulmonary diseases (tuberculosis, asthma, etc) |  |  |
| 9 | Patients who are likely to worsen or planed ICU admission or ventilator support due to any reason |  |  |
| 10 | Pregnancy and lactation |  |  |
| 11 | Participation in a drug interventional clinical drug trial of any nature in the 3 month period preceding onset of COVID-19 |  |  |
| 12 | Participation in any other clinical trial of an experimental agent treatment for COVID-19 |  |  |
| 13 | Patients on any kind of Ayurveda treatment or any other alternative and complementary medicinal systems such as Homeopathy, Unani, Siddha and in particular requiring oral therapy of any kind. |  |  |
| 14 | Physician decision that involvement in the study is not in the patient´s best interest |  |  |

[figure not shown]

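### Eligibility is stated inconsistently: the diagnosis rule, the age range and the CRF checklist disagree, so the same patient can be eligible or a protocol violation depending on the page read

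*Combined protocol and SAP*

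**What the plan says.** **Diagnosis.** Synopsis item h describes the population as laboratory-confirmed. Synopsis item i and Section 10 share one criterion: "Typical Clinical presentation of acute onset febrile illness with cough and a RT_PCR based laboratory confirmation test for COVID-19". The section on consent, selection, screening and enrolment prefers a positive RT-PCR but adds that "a patient with a clinical diagnosis of COVID- 19 as described below will be eligible". The CRF checklist in Appendix H repeats the RT-PCR criterion as item 1. Item 2 then covers typical illness in someone from a hot-spot area or "in close contact with a confirmed COVID 19 case with a negative laboratory test for COVID 19 and H1N1 influenza". The two items stand in one yes/no list with no connecting word.

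**Age.** The synopsis has "Patients with either sex, 18 to 75 years age", and the CRF agrees. Section 10 has "Patients with either sex, 21to 69years age".

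**Items found in one place only.** The CRF excludes patients with "At least one fever every 24 hours for > 72h", which is in neither the synopsis nor Section 10. The CRF also has a blood-donation inclusion item that the other two lack. Section 10 excludes patients receiving another test drug, an item absent from the synopsis and CRF.

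**Severity.** The synopsis and CRF define severe disease by at least two of three criteria. Section 10 leaves it to the physician and offers the same three as guidance. More than an hour of oxygen support is among the examples there, yet Section 3 says: "Mere need for supplement oxygen using non-invasive means will not negate the classification of mild to moderate COVID-19". The first stop rule in Section 14 points back to the exclusion criteria for its meaning of severe.

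**The concern.** Eligibility decides who is randomised, who counts as a protocol violation and whom the result describes. Section 18.1 allows no deviation except in an emergency, and the synopsis promises both an intent-to-treat and a per-protocol completer analysis. Neither works cleanly if the protocol does not settle who was eligible. The CRF matters most in practice, because its pages direct site staff to that checklist.

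The diagnosis conflict also bears on the treatment comparison. A patient admitted on a negative test may not have the disease under study. Such patients could pull the estimated effect towards zero. They could also meet the first secondary outcome, RT-PCR negativity, whatever treatment they received. The age conflict is different in kind: it affects generalisability and the count of violations, not dilution.

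**Working it through.** **Step 1. The four statements side by side.**

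| Place | Diagnosis | Age | Daily fever over 72 h excludes? | Severe disease |
|---|---|---|---|---|
| Synopsis, items h and i | Laboratory / RT-PCR confirmed | 18–75 | No | At least two of three criteria |
| Enrolment section | RT-PCR preferable; clinical diagnosis accepted | None given | Not stated | Refers to the criteria elsewhere |
| Section 10 | RT-PCR confirmed | 21–69 | No | Physician judgement with guidance |
| CRF, Appendix H | RT-PCR (item 1), and a negative-test item (item 2) | 18–75 | Yes | At least two of three criteria |

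**Step 2. Test cases** (each otherwise eligible).

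- RT-PCR positive, aged 72 or 19: eligible under the synopsis and CRF, ineligible under Section 10.
- Aged 40, close contact, typical illness, negative test: ineligible under the synopsis and Section 10. CRF item 2 fits. The enrolment section may fit, but its promised definition never appears in the body.
- Aged 40, RT-PCR positive, daily fever for four days: eligible under the synopsis and Section 10, excluded by the CRF.
- One of the three severity criteria only: not severe under the synopsis and CRF, but open to exclusion on judgement under Section 10.

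**Step 3. Possible dilution.** The plan has no figure to reproduce. Section 17.1 sets 70 per arm by consensus, without a power calculation, and gives no effect size. The following is illustration only. Let *f* be the fraction of enrolled patients who cannot benefit. This is an assumption; the documents give no value. With SD and control rate unchanged, the effect becomes (1 − *f*) times its full size, and the sample size for fixed power rises by 1/(1 − *f*)².

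- Reference effect: the standardised difference with 80% power at 70 per arm and two-sided 0.05 is (1.960 + 0.842) × √(2/70) = 0.474.
- Diluted power: Φ(2.802 × (1 − *f*) − 1.960).

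| *f* | Inflation of n | n per arm for 80% power | Power at 70 per arm |
|---|---|---|---|
| 10% | 1/0.9² = 1.23 | 87 | 71.3% |
| 20% | 1/0.8² = 1.56 | 110 | 61.1% |
| 30% | 1/0.7² = 2.04 | 143 | 50.0% |

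For recovery proportions, assume 70% against 90% with 70 per arm. Power is then 84.9% at *f* = 0 and 74.9%, 63.0% and 50.3% at 10%, 20% and 30%.

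**Step 4. Sensitivity to the zero-benefit assumption.** If test-negative patients keep a fraction *r* of the benefit, the multiplier on the effect is 1 − *f*(1 − *r*). With *f* = 20% and *r* = 0.5 it is 1 − 0.20 × 0.5 = 0.90, so the inflation is 1.23 instead of 1.56.

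**The case against.** The best defence is that the enrolment section itself sends patients to be screened against the protocol's inclusion and exclusion criteria, so Section 10 governs and the rest is drafting residue. All sites hold the same document, and Section 19.12 promises meetings and SOPs for uniformity. This softens the practical risk. It does not remove the conflict: the same section then widens the diagnosis rule, Section 19.12 does not mention eligibility, and the checklist sites complete disagrees with Section 10.

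Several stronger readings are tempting, and the documents do not support them:

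- *The enrolment section admits PCR-negative patients aged 18 to 75.* It gives no age and does not mention a negative test. The wider age range is in the synopsis and CRF; the negative-test route is only in the CRF.
- *CRF items 1 and 2 make enrolment impossible.* They read more naturally as alternatives with the word *or* missing.
- *Test-negative entrants score as virological successes at baseline.* That outcome is tested later, from clinical recovery or the tenth day of symptoms, whichever is earlier. They may meet it then regardless of treatment.
- *Sites will enrol different populations and the effect will be diluted by a known amount.* Both are inference. No share is given, and Appendix O notes that poor sampling can produce a false negative. Zero benefit is not established either, since Section 3.1 cites an influenza-like-illness pilot in support of AYUSH 64.
- *Sections 3 and 10 flatly contradict each other on oxygen.* Section 10 offers its list as guidance in progressive respiratory failure, and its own note speaks of invasive oxygen techniques. This is an ambiguity.

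**Conclusion.** The point stands as an inconsistency in the current text that must be corrected. Diagnosis and age are stated in incompatible ways, the CRF adds a fever exclusion with no counterpart in the synopsis or Section 10, and the clinical diagnosis accepted at enrolment is never defined in the body. The certain consequences are that a patient's eligibility depends on the page consulted and that the per-protocol set is ill-defined. Dilution and easier attainment of the later PCR-negativity outcome are possible, not demonstrated. The inflation of 1.23 to 2.04 rests on an assumed *f* of 10% to 30% and on no benefit in those patients, and it alters no figure in the plan. The severity and oxygen wording is ambiguous rather than contradictory, but it matters because a stop rule depends on it.

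**What to change.** Keep one master eligibility list in Section 10, with one diagnosis rule and one age range. Copy it verbatim to the synopsis, the enrolment section and the CRF. State whether the fever item applies, and settle the other items that appear in only one list.

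On diagnosis, take one of two routes:

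1. Align the enrolment sentence and CRF item 2 with the RT-PCR requirement.
2. Keep clinically diagnosed patients, but define them in the body. Make the primary analysis the patients positive on the pre-randomisation swab, with all randomised patients as a supporting analysis. Because the swab precedes allocation, this keeps the randomised comparison intact.

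Fig 1 already lists a baseline PCR. The Appendix A schedule has no row for it, so one should be added, with the swab dated before randomisation.

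The sponsor must reconcile the wording on severity, oxygen and withdrawal in the synopsis, Sections 3, 10 and 14 and the CRF. No clinical rule or age limit is proposed here.

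The cost is wording in the protocol and CRF, with possibly slower enrolment under the first route or a somewhat smaller primary analysis set under the second.

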**f. Study design:**

This is a prospective, randomized, open label, blinded end point (PROBE), parallel efficacy, multicentric, two arm study to compare the efficacy of a combination of Standard of Care (SOC) plus a selected individual Ayurveda herbal drug (Samshamani Vati Plus or AYUSH 64 or Yashtimadhu) to SOC (active control). The Ayurveda drug is being considered as an adjunctive or an add-on therapy and each of the three drugs will be evaluated in separate two arm trial with a common study design. The drug trials are ‘exploratory’ in design. The Study Flow diagram summarizes the study design and schedule of events (Fig 1) (Appendix A).

**g. Sample size:** The total sample size is 140 patients per drug trial- 70 patients in each arm.

**h. Study Population:** All adult patients with laboratory-confirmed SARS-CoV2 infection with mild to moderate category will be selected from the outpatient or inpatient facility in COVID-19 medical centers/hospitals. Voluntary patients will be explained about the study and if willing will sign the informed consent and be screened for eligibility.

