**Criteria of ‘Clinical Recovery’**:

1. Normal body temperature (≤36.6°C axilla or ≤37.2 °C oral)
2. Absence of cough or mild cough (infrequent, short episodic, non-wheezy, relieved by minimal or no medication, not interfering with routine speech and not related to lying in bed, mild sore throat or nasal congestion)
3. Absence of breathlessness on routine daily self-care chore or respiratory rate less than 30 breaths per minute without supplemental oxygen
4. Absence of any other symptom/sign attributed to COVID-19 illness
5. Normalization of SpO2 by standard peripheral oximetry device (above 95 percent)
6. Recovery should be sustained for at least 48 hours under physician observation
7. Assessed by physician blinded to treatment allocation
8. All of the above criteria ought to be fulfilled

Note: Clinical recovery would be deemed from the first day of satisfying the above criteria

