# 17. STATISTICAL DESIGN, SAMPLE SIZE ANDANALYSIS, DATA BASE

As described above, there are 3 Ayurveda plant formulations and each will be tested separately for clinical efficacy and safety as an adjunct/add-on therapy to the SOC in patients suffering from mild to moderate COVID-19 in a non-randomized, open label, parallel efficacy, active control study; active control being the arm with only SOC. The study design is exploratory in nature. This protocol will be used by each of the selected Ayurveda formulations in standalone drug trial evaluation study and in different sites.

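### The enrolling investigator holds the randomization table and performs the allocation in an open-label trial, with no concealment step described

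*Combined protocol and SAP*

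**What the plan says.** The section headed Consent, Selection, Screening, and Enrollment sets out the allocation procedure: "Eligible patients will be enrolled using a simple randomization table (provided to the investigator) in a block of 20 patients each". It continues: "As the target sample size is 70 patients in each arm, the first block of randomized allocation will be of 10". It ends with: "The study randomization will be carried out by the investigator".

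The synopsis (item f) states the masking: "This is a prospective, randomized, open label, blinded end point (PROBE), parallel efficacy, multicentric, two arm study". Blinding is described in two places. One criterion for clinical recovery, in the synopsis and in Section 11.1, reads "Assessed by physician blinded to treatment allocation". The section on clinical evaluation has a paramedic complete several questionnaires without knowing the allocation.

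The opening paragraph of Section 17 describes each trial as conducted "in a non-randomized, open label, parallel efficacy, active control study; active control being the arm with only SOC". The study title, synopsis items f and n, Section 5 and the enrolment section itself all say randomized.

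**The concern.** Random allocation protects the comparison only if the person deciding whether and when to enter a patient cannot see the next assignment. Here the table is "using a simple randomization table (provided to the investigator"), and the same role carries out the allocation. In an open-label trial each assignment also becomes visible once made, so past allocations add information about the rest of a block.

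Entry leaves room for judgement. The exclusion criteria in Section 10 have severe disease judged by a physician, exclude patients thought likely to worsen, and allow exclusion when a physician decides that participation is not in the patient's best interest. The enrolment section also accepts a clinical diagnosis without a positive RT-PCR, whereas the first inclusion criterion in Section 10 asks for laboratory confirmation. An investigator who knows the next assignment could, without intending to, let it influence any of these decisions or the moment of enrolment. Prognosis at entry bears directly on the primary outcome, days to clinical recovery. An imbalance created this way would look like a treatment effect, and adjustment could remove only the part that is measured.

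**Working it through.** **Step 1. Custody and safeguards, set side by side.**

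- Who holds the list: the investigator (enrolment section).
- Who allocates: the investigator (enrolment section).
- Who explains the study and takes consent: the investigator (Section 20.5).
- Treatment masking: none, the trial is open label (title, synopsis item f, Section 5).
- Blinding: recovery assessment and some questionnaires. Both act after allocation.
- Order of enrolment: first come, first served (enrolment section). This does not control who is approached or who is judged eligible.
- Concealment (independent holder, envelopes, central release, registration before reveal): none described.
- Standard operating procedures: mentioned in Section 19.12 as complementing the protocol. Their content is not given.

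The gap in concealment is therefore more than silence. The plan positively assigns the table to the person from whom it should be withheld.

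**Step 2. Block arithmetic.** The stated total reproduces: 2 x 70 = 140.

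- If 20 counts patients in total: 140/20 = 7 full blocks, so no block of 10 is needed. Starting with 10 leaves 130/20 = 6.5 blocks, which does not close.
- If 20 counts patients per arm: 10 + 3 x 20 = 70, which closes exactly.

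The wording is ambiguous. The per-arm reading explains the first block of 10. The method is also called simple although it is blocked.

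**Step 3. How much concealment would change.** Assume one list, 1:1 permuted blocks, and an enroller who knows the block size and all past assignments. For a block of 2m patients, the expected number of assignments known with certainty is 2m/(m+1). The expected number of correct guesses, always guessing the arm with more places left, is m + 2^(2m-1)/C(2m,m) - 1/2.

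- Table readable: 140/140 = 100% can be foreseen.
- Concealed, seven blocks of 20 in total (m = 10): certain 7 x 20/11 = 12.7, and 12.7/140 = 9.1%. Correct guesses are 12.34 per block, or 12.34/20 = 61.7%.
- Concealed, per-arm reading (one block of 20 in total, then three of 40; m = 10, then m = 20): certain 20/11 + 3 x 40/21 = 1.82 + 5.71 = 7.5, and 7.5/140 = 5.4%. Correct guesses are 12.34 + 3 x 23.49 = 82.8, and 82.8/140 = 59.1%.

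The documents do not say whether there is one list or one per site. Site lists would change the last two results.

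**Step 4. A hypothetical illustration of bias.** Table 2 cites a recovery interquartile range of 7 to 14 days from one hospital cohort, giving SD = (14 - 7)/1.349 = 5.2 days and SE = 5.2 x sqrt(2/70) = 0.88 day. Suppose mild and moderate patients differ by 4 to 6 days and the arms differ by 20 to 30 percentage points in severity mix. Neither range is in the documents.

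- 20-point shift: bias 0.2 x 4 = 0.8 to 0.2 x 6 = 1.2 days. Two-sided rejection at 0.05 with no true effect is 0.149 to 0.276.
- 30-point shift: bias 0.3 x 4 = 1.2 to 0.3 x 6 = 1.8 days. Rejection is 0.276 to 0.535.

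These figures show what such a shift would do if it occurred. They do not estimate its likelihood.

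**The case against.** **Foreknowledge is inferred.** The protocol does not say whether the table is open or masked, or when it is consulted, and unseen operating procedures might add a safeguard. A reader might infer that every assignment is in fact known before enrolment. The documents support only that assignments can be known and that no concealment is described. That suffices for the point, because the written rule hands over the table.

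**Roles are less concentrated than they may appear.** Standard care is decided by the treating physician (Section 5), study physicians act alongside that physician (Fig 1), and each site has at least two principal investigators. It would go too far to say that the list holder also treats the patient. The physician judging severity is not named as the holder either, although nothing separates the two roles.

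**Judgement at entry is bounded.** Mild and moderate patients are both eligible, so that distinction does not decide entry, and the severe cut-off has numeric guides (30 breaths per minute, SpO2 93%). This stands. The discretion lies in the likely-to-worsen and best-interest exclusions and in the clinical-diagnosis route.

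**The illustration is weakly anchored.** This also stands. Only the SD has a source, and it comes from a retrospective single-centre cohort in which 20% had ARDS (Table 3). The case record form records mild or moderate status on admission, so adjustment could largely remove the imbalance modelled. It could not remove imbalance in unmeasured prognosis.

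**Block size.** A reader might count large blocks as part of the fault. Larger blocks are harder to predict than small ones, and the first block differs from the rest, so the blocks are not of one fixed size. Site stratification and other block sizes are preferences in a trial of 140 patients that calls itself exploratory.

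**The exploratory label** does not dispose of the concern. Synopsis item n prespecifies two-sided p<0.05 and expects meaningful conclusions, and selection bias does not shrink because a trial is exploratory.

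**Conclusion.** The concern holds as a defect of procedure. The plan gives the table to the investigator, has the investigator allocate, and describes nothing that hides the next assignment. Neither blinded assessment nor first-come enrolment closes that gap. The exposure is up to 140 of 140 assignments if the table can be read, against about 5-9% certain under concealment with the same blocks, given the single-list assumptions above. The resulting bias cannot be quantified from the documents. The 15-54% type I error range is hypothetical, since both the severity gap and the imbalance are assumed, and the conclusion does not depend on it.

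A reader might take Section 17's "in a non-randomized, open label, parallel efficacy, active control study" as evidence that patients will not be randomized, or as support for the concealment point. It is neither. It stands alone against the title, synopsis, Section 5 and the enrolment section, and is most likely a drafting slip. It still needs correcting because it sits in the section that governs the analysis.

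The allocation procedure should be changed before the first patient is enrolled, since concealment cannot be restored afterwards.

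**What to change.** In the enrolment section:

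- State that the list is generated and held by someone independent of enrolment, and withdraw the table from investigators.
- Reveal each assignment only after consent, eligibility and baseline data have been registered. Use central release by phone, SMS or App, or centrally prepared, sequentially numbered, opaque sealed envelopes.
- Keep block sizes out of the site-facing protocol. In a restricted document, state whether 20 and the first block of 10 count patients in total or per arm, and replace the word simple with a description of the blocked method.
- Site stratification and varied block sizes are optional.

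In Section 17, change non-randomized to randomized.

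Cost: protocol wording, a short allocation procedure, a short delay per enrolment and a small central task. The Central Monitoring Cell of Section 19.3 could release assignments, but it is planned to receive participants' daily App responses and has no allocation role, so this would be an added function. The sample size stays at 140 per trial.
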